## Abstract

**Background:**

Scientific hypothesis generation is a critical step in scientific research that determines the direction and impact of any investigation. Despite its vital role, we have limited knowledge of the process itself, thus hindering our ability to address some critical questions.

**Objective:**

This study aims to answer the following questions: To what extent can secondary data analytics tools facilitate the generation of scientific hypotheses during clinical research? Are the processes similar in developing clinical diagnoses during clinical practice and developing scientific hypotheses for clinical research projects? Furthermore, this study explores the process of scientific hypothesis generation in the context of clinical research. It was designed to compare the role of VIADS, a visual interactive analysis tool for filtering and summarizing large data sets coded with hierarchical terminologies, and the experience levels of study participants during the scientific hypothesis generation process.

**Methods:**

This manuscript introduces a study design. Experienced and inexperienced clinical researchers are being recruited since July 2021 to take part in this 2×2 factorial study, in which all participants use the same data sets during scientific hypothesis–generation sessions and follow predetermined scripts. The clinical researchers are separated into experienced or inexperienced groups based on predetermined criteria and are then randomly assigned into groups that use and do not use VIADS via block randomization. The study sessions, screen activities, and audio recordings of participants are captured. Participants use the think-aloud protocol during the study sessions. After each study session, every participant is given a follow-up survey, with participants using VIADS completing an additional modified System Usability Scale survey. A panel of clinical research experts will assess the scientific hypotheses generated by participants based on predeveloped metrics. All data will be anonymized, transcribed, aggregated, and analyzed.

**Results:**

Data collection for this study began in July 2021. Recruitment uses a brief online survey. The preliminary results showed that study participants can generate a few to over a dozen scientific hypotheses during a 2-hour study session, regardless of whether they used VIADS or other analytics tools. A metric to more accurately, comprehensively, and consistently assess scientific hypotheses within a clinical research context has been developed.

**Conclusions:**

The scientific hypothesis–generation process is an advanced cognitive activity and a complex process. Our results so far show that clinical researchers can quickly generate initial scientific hypotheses based on data sets and prior experience. However, refining these scientific hypotheses is a much more time-consuming activity. To uncover the fundamental mechanisms underlying the generation of scientific hypotheses, we need breakthroughs that can capture thinking processes more precisely.

**International Registered Report Identifier (IRRID):**

DERR1-10.2196/39414

## Introduction

A hypothesis is an educated guess or statement about the relationship between 2 or more variables [1,2]. Scientific hypothesis generation is a critical step in scientific research that determines the direction and impact of research investigations. However, despite its vital role, we do not know the answers to some basic questions about the generation process. Some examples are as follows: “Can secondary data analytics tools facilitate the process?” and “Is the scientific hypothesis generation process for clinical research questions similar to differential diagnosis questions?” Traditionally, the scientific method involves delineating a research question and generating a scientific hypothesis. After formulating a scientific hypothesis, researchers design studies to test the scientific hypothesis to determine the answers to research questions [1,3].

Scientific hypothesis generation and scientific hypothesis testing are distinct processes [1,4]. In clinical research, research questions are often delineated without the support of systematic data analysis and are not data driven [1,5,6]. Using and analyzing existing data to facilitate scientific hypothesis generation is considered ecological research [7,8]. An ever-increasing amount of electronic health care data is becoming available, much of which is coded. These data can be a rich source for secondary data analysis, accelerating scientific discoveries [9]. Thus, many researchers have been exploring data-driven scientific hypothesis generation guided by secondary data analysis [1,10]. This includes various fields, including genomics [4]. However, exactly how a scientific hypothesis is generated, even as shown by secondary data analysis in clinical research, is unknown. Understanding the detailed process of scientific hypothesis generation could improve the efficiency of delineating clinical research questions and, consequently, clinical research. Therefore, this study investigates the process of formulating scientific hypotheses guided by secondary data analysis. Using these results as a baseline, we plan to explore ways of supporting and improving the scientific hypothesis–generation process and to study the process of formulating research questions as long-term goals.

Electronic health record systems and related technologies have been widely adopted in both office-based physician practices (86% in 2019) [11] and hospitals (overall 86% in 2022), and types vary based on hospital types [12] across the United States. Thus, vast amounts of electronic data are continuously captured and available for analysis to guide future decisions, uncover new patterns, or identify new paradigms in medicine. Much of the data is coded using hierarchical terminologies, and some of these commonly used terminologies include the International Classification of Diseases, 9th Revision-Clinical Modification (ICD9-CM) [13] and 10th Revision-Clinical Modification (ICD10-CM) [14], Systematized Nomenclature of Medicine-Clinical Terms (SNOMED-CT) [15], Logical Observation Identifiers Names and Codes (LOINC) [16], RxNorm [17], Gene Ontology [18], and Medical Subject Headings (MeSH) [19]. We used the coded data sets by hierarchical terminologies *as examples* of existing data sets to facilitate and articulate the scientific hypothesis–generation process in clinical research, especially when guided by secondary data analyses. Algorithms [20,21] and a web-based secondary data analytics tool [22-25] were developed to use the coded electronic data (ICD9 or MeSH) in order to conduct population studies and other clinically relevant studies.

Arocha et al and Patel et al [26,27] studied the directionality of reasoning in scientific hypothesis–generation processes and evaluation strategies (of confirmation or disconfirmation) for solving a cardiovascular diagnostic problem by medical students (novice) and medical residents (experienced). The reasoning directions include forward (from evidence to a scientific hypothesis) and backward (from a scientific hypothesis to evidence). More experienced clinicians used their own underlying situational knowledge about the clinical condition, while the novices used the surface structure of the patient information during the diagnosis generation process. The studies by Patel et al [28,29] and Kushniruk et al [30] used inexperienced and experienced clinicians with different roles, levels of medical expertise, and corresponding strategies to diagnose an endocrine disorder. In these studies, expert physicians used more efficient strategies (integrating patient history and experts’ prior knowledge) to make diagnostic decisions [28,30,31]. All these studies focused on hypothesis generation in solving diagnostic problems. Their results set the groundwork for reasoning in the medical diagnostic process. Their findings regarding the generation of diagnostic hypotheses by experienced and inexperienced clinicians via different processes helped us formulate and narrow our research questions. Their methodology involved performing predefined tasks, recording “think-aloud” sessions, and transcribing and analyzing the study sessions. Making a diagnosis is a critical component of medicine and a routine task for physicians. In contrast, generating scientific hypotheses in clinical research focuses on establishing a scientific hypothesis or doing further searches to explore alternative scientific hypotheses for research. The difference between the 2 can be demonstrated by 2 enterprises. In clinical practice, the goal of generating a diagnostic hypothesis is to make decisions about patient care and the task is time constrained, while in scientific research, time is not similarly constrained and the task is to explore various scientific hypotheses to formulate and refine the final research question. In both making a medical diagnosis in clinical practice and scientific thinking, generating initial hypotheses depends on prior knowledge and experience [32,33]. However, in scientific thinking, analogies and associations play significant roles, in addition to prior knowledge, experience, and reasoning capability. Analogies are widely recognized as playing vital heuristic roles as aids to discovery [32,34], and these have been employed in a wide variety of settings and have had considerable success in generating insights and formulating possible solutions to existing problems.

This makes it essential to understand the scientific hypothesis–generation process in clinical research and to compare this process with generating clinical diagnoses, including the role of experience during the scientific hypothesis–generation process.

This study explores the scientific hypothesis–generation process in clinical research. It investigates whether a secondary data analytics tool and clinician experience influence the scientific hypothesis–generation process. We propose to use direct observations, think-aloud methods with video capture, follow-up inquiries and interview questions, and surveys to capture the participants’ perceptions of the scientific hypothesis–generation process and associated factors. The qualitative data generated will be transcribed, analyzed, and quantified.

We aim to test the following study hypotheses:

Experienced and inexperienced clinical researchers will differ in generating scientific hypotheses guided by secondary data analysis.Clinical researchers will generate different scientific hypotheses with and without using a secondary data analytics tool.Researchers’ levels of experience and use of secondary data analytics tools will interact in their scientific hypothesis–generation process.

In this paper, we used the term “research hypothesis” to refer to a statement generated by our research participants, the term “study hypothesis” to refer to the subject of our research study, and the term “scientific hypothesis” to refer to the general term “hypothesis” in research contexts.

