### Participants and Recruitment

Experienced and inexperienced clinical researchers, and a panel of clinical research experts, have been recruited for this study. The primary criterion used to distinguish subjects in the 3 groups is the level of their experience in clinical research. Table 1 summarizes the requirements for clinical researchers, expert panel members, and the computers that clinical researchers use during the study sessions. Participants are compensated for their time according to professional organization guidelines.

**Table 1 table1:** Summary of the criteria for study participants and clinical research expert panel members.

Variable	Inexperienced clinical researchers^a^	Experienced clinical researchers^a^	A panel of clinical research experts
Participation in research hypothesis generation and study design	≤2 years	Leading role ≥5 and <10 years	Leading role ≥10 years
Participation in data analysis of study results	≤2 years	Leading role ≥5 and <10 years	Leading role ≥10 years
Publications in clinical research	Not required	≥5 as a leading author, including first, correspondence, or senior author for original studies	≥10 as a leading author, including at least one article in a high-impact journal in the past 5 years
Review experience in clinical research for conferences, journals, or grants	Not required	Not required	≥10 years
Internet connection	Required	Required	Required
Microphone	Required	Required	Not required
Software package for data analysis (eg, Microsoft Excel and R)	Required	Required	Not required
Tools to facilitate research hypothesis generation, if available	Required	Required	Not required

^a^If a participant has clinical research experience between 2 and 5 years, the decisive factor for the experienced group will be 5 publications for original studies as the leading author.

To recruit participants, invitational emails and flyers have been sent to collaborators, along with other communication means, including mailing lists, such as those of working groups of the American Medical Informatics Association, South Carolina Clinical & Translational Research Institute newsletters, and PRISMA health research newsletters, and Slack channels, such as National COVID Cohort Collaborative communities. All study sessions are conducted remotely via video conference software (Webex, Cisco) and recorded via a commercial software (BB FlashBack, Blueberry Software).

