### Study Design

Study 1 tests all 3 study hypotheses. If the study hypotheses are supported in Study 1, we will conduct a follow-up study (Study 2) to examine whether and how the efficiency or quality of research hypothesis generation may be improved or refined.

We will use the think-aloud method to conduct the following tasks: (1) observe the research hypothesis–generation process; (2) transcribe data, and analyze and assess if VIADS [22] and different levels of experience of clinical researchers influence the process; and (3) assess the interactions between VIADS (as an example of a secondary analytical tool) and the experience levels of the participants during the process. Figure 3 summarizes the Study 1 and Study 2 procedures.

#### Study 1

Experienced and inexperienced clinical researchers conduct research hypothesis–generation tasks using the same secondary data sets. The tasks are captured to describe participants’ research hypothesis–generation processes when guided by analysis of the same data sets. VIADS is also used as an example of a secondary data analytics tool to assess participants’ research hypothesis–generation processes. Accordingly, 2 control groups do not use VIADS, while 2 intervention groups do use it.

A pilot study, Study 0, was conducted in July and August 2021 for each group to assess the feasibility of using the task flow, data sets, screen capture, audio and video recordings, and study scripts. In Study 1, 4 groups are utilized. Table 3 summarizes the study design and participants in each group. The 4 groups will be compared in order to detect the primary effects of the 2 factors and their interactions after completing Study 1. After recruitment, the participants are separated into experienced or inexperienced groups based on predetermined criteria. Then, the participants are randomly assigned to a group that uses VIADS (3-hour session, with 1 hour to conduct VIADS training) or does not use VIADS (2-hour session) via block randomization.

**Table 3 table3:** Design of Study 1 for assessment of the hypothesis–generation process in clinical research.

Variable	Number of experienced clinical researchers	Number of inexperienced clinical researchers
Not using VIADS	8 (Group 1)	8 (Group 2)
Using VIADS	8 (Group 3)	8 (Group 4)

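### The objective and hypotheses 2 and 3 speak of analytics tools in general, but the randomised contrast is VIADS plus 1 hour of training added to own software versus own software alone

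*Protocol article*

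**What the plan says.** **The question.** The Objective in the abstract opens with "To what extent can secondary data analytics tools facilitate the generation of scientific hypotheses during clinical research". In the Introduction, hypothesis 2 is "Clinical researchers will generate different scientific hypotheses with and without using a secondary data analytics tool", and hypothesis 3 concerns the interaction of experience with use of such tools.

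**The factor.** Under Study 1, "2 control groups do not use VIADS, while 2 intervention groups do use it". Allocation is by chance between two conditions, worded as "uses VIADS (3-hour session, with 1 hour to conduct VIADS training) or does not use VIADS (2-hour session) via block randomization". Table 3 labels its rows by VIADS use, and the Data and Statistical Analysis section names VIADS and experience as the two ANOVA factors. The article presents VIADS as one example of a secondary data analytics tool.

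**What every participant has.** Table 1 marks as required, for both inexperienced and experienced researchers, the item "Software package for data analysis (eg, Microsoft Excel and R" and the item "Tools to facilitate research hypothesis generation, if available". The table is laid out by experience level and makes no exception for either randomised arm. The abstract's Results describe sessions as productive "regardless of whether they used VIADS or other analytics tools".

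**What was seen.** Under Initial Observations, the article reports that VIADS training raised cognitive load, and that many participants used no advanced analysis. The second remark is not broken down by arm.

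**The concern.** A reader of hypothesis 2 expects a control group without an analytics tool. The controls here are defined only by not using VIADS, and they are required to have analysis software of their own. The arms also differ in a second respect, an hour of training given to one arm only, which the authors themselves name as a possible influence.

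What is at stake is interpretation. A positive VIADS effect could be credited to analytics tools as a class, or to the software apart from its training, and the design supports neither attribution. A null effect could be taken as an answer to the objective about tools in general, although both arms had analysis software to hand. Hypothesis 3 inherits the problem, because its interaction term uses the same VIADS factor.

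**Working it through.** The question is which contrast is estimated, so the main check sets the texts side by side.

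| Element | VIADS arms (Groups 3, 4) | Control arms (Groups 1, 2) | Source |
|---|---|---|---|
| VIADS | yes | no | Study 1, Table 3 |
| Own analysis software | required | required | Table 1 |
| Hypothesis-generation tools, if available | required | required | Table 1 |
| Training | 1 hour | none described | Study 1 |
| Session length | 3 hours | 2 hours | Study 1 |
| Time left for the task | 3 − 1 = 2 hours | 2 hours | arithmetic |

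Step 1. Remove what the arms share. Own software and any available hypothesis-generation tools are in both columns, and so are the 2 hours of task time.

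Step 2. Two differences remain: VIADS and its training. They always occur together.

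Step 3. The VIADS main effect is therefore (own software + VIADS + training) − (own software). It contains no comparison with a group lacking analysis software, and no term that varies VIADS while holding training fixed.

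**The plan's own figure.** The stated sample size is 32 (α=.05, f=0.5, power 0.8). For a 1-df effect in four groups, take the noncentral F with λ = f²N = 0.25 × 32 = 8 and df (1, 28). Power is 0.779, and the smallest N reaching 0.80 is 34 (power 0.805). The normal approximation gives 16 per factor level, hence 32. The figure thus reproduces closely, and it is untouched by this point.

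**Illustration only.** Suppose the planned f=0.5, which is 1 SD between two levels, were meant as the effect of a tool against no tool. Suppose also that a share s of controls got the full benefit from their own software. The visible effect is then (1 − s) SD, with f = 0.5(1 − s):

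| Assumed s | f | λ | Power at N=32 |
|---|---|---|---|
| 0 | 0.5 | 8 | 78% |
| 0.25 | 0.375 | 4.5 | 54% |
| 0.50 | 0.25 | 2 | 28% |

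The documents give no value for s. Nor do they say that f=0.5 referred to tool against no tool.

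**The case against.** The design sections name the factor correctly. The Objective itself goes on to say the study compares the role of VIADS, VIADS is openly called an example, and Table 3 and the ANOVA refer to VIADS. No sentence calls the controls tool-free. This stands, and it places the fault in the wording of the objective and of hypotheses 2 and 3, not in the analysis. It does not remove the fault: using one member of a class as the intervention does not turn controls who have other members of that class into a group without a tool.

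Training is a natural part of introducing unfamiliar software, task time is equal, and the cognitive-load issue is disclosed. This also stands. A bundled intervention is legitimate, provided the claim names the bundle.

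Three stronger readings may tempt a reader, and the documents support none of them.

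- *The trial compares VIADS with own software.* Table 1 gives own software to both arms, so VIADS is added to it and does not replace it.
- *Controls in effect had the full benefit of an analytics tool, so power collapses.* Having software does not show that it was used for analysis. The abstract's remark about other tools gives no counts, and many participants are reported to have used no advanced analysis. The power table above rests on assumption alone.
- *A null result will be reported as tools not helping.* The article does not say so. Its Study 2 section says that, if no VIADS difference is found, VIADS will be revised from the usability and utility results and Study 2 will not be conducted.

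**Conclusion.** The point holds as a mismatch between the question as worded and the contrast as randomised. It affects the first objective and hypotheses 2 and 3; hypothesis 1 is not touched. The trial can estimate the effect of VIADS with 1 hour of training, added to the participant's own software, against own software alone. It cannot answer whether analytics tools as a class help compared with none, and it cannot separate VIADS from its training.

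This rests on two readings: that the software requirement in Table 1 applies to both randomised arms, as printed, and that controls received no comparable training, since none is described. The size of any dilution is unknown, because the article does not report how much analysis software the controls actually used. The consequence lies in what may be concluded; no sample size, test or stated figure has to change. The article says analysis of the think-aloud data had not begun and that sessions were still incomplete, so the wording can still be corrected ahead of the results.

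**What to change.** 1. Restate the first objective and hypotheses 2 and 3 in terms of VIADS with 1 hour of same-day training, in addition to the participant's own software, versus own software alone.
2. Limit conclusions to that contrast, whether the result is positive or null. Make no general statement about secondary data analytics tools, and none about VIADS apart from its training.
3. From the screen recordings already being made, code which software each participant actually used and report it descriptively by arm. Do not present outcomes by software used as a causal subgroup comparison: use is not randomised, it occurs after assignment, and each cell has 8 participants.
4. If the effect of control software use on power is discussed at all, show it as an assumed range.

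The cost is a narrower claim, a few sentences of rewording and one coded variable. No new arm, participant or test is needed.
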